#### Collaborative Approach

In collaboration with other data sharing registries, researchers can find patterns, trends, and potential treatments for fungal infections by pooling their data more efficiently. Similar to other registries, it encourages teamwork in problem-solving and may result in more efficient diagnosis, treatment, and prevention approaches [25,26]. For surveillance of neglected tropical diseases, a database of mycetoma and chromoblastomycosis will help to identify different nodal areas for future surveillance through active case searches.

#### One Health Approach

Fungi are ubiquitous. Their interaction with agriculture and animals is certain. As part of the “One Health” concept, keeping in view the data of drug-resistant fungi reported through the registry, we can further collaborate with the Indian Council of Agricultural Research and Indian Veterinary Research Institute (both under the Ministry of Agriculture and Farmer Welfare) to study the effect of use of different fungicides in agriculture and animals and study the transmission dynamics within these.

### Conclusions

IFIs are hidden ICU killers. Unfortunately, in a tropical country such as India with a high potential population for fungal infections, mycology is still a neglected area. The present recommendations mostly rely on a compilation of case reports, studies from specific medical facilities, and professional judgments. Analyses must be performed on a large cohort of patients to make treatment recommendations based on sound evidence. It is imperative to explore the contribution of opportunistic fungal infections in the morbidity and mortality of immunocompromised patients and determine the frequency of occurrence of this condition in the country by establishing a registry. Therefore, the development of a Mycology Clinical Registry through the established ICMR-MycoNet centers is proposed to improve the lack of knowledge on epidemiology, clinical course-biology, pathology mechanisms of IFIs and their trends, and AFST and to aid in facilitating an evidence-based diagnostic therapeutic integrated approach to IFI. Antifungal stewardship through this unique initiative will help to reduce empirical antifungal therapy. Any emerging threats, such as the spread of resistant strains or outbreak signals, can be picked up quickly through this real-time database for quick action and policy decisions. These state-of-the-art facilities will be the game changers and able to find cryptic fungal cases successfully, which will visibly change the public health profile of the country.

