**Objective:**

The primary aim of this study is to create a multicenter digital clinical registry and monitor trends of IFIs and emerging fungal diseases, as well as early signals of any potential fungal outbreak in any region. The registry will also capture information on the antifungal resistance patterns and the contribution of fungal infections on overall morbidity and inpatient mortality across various conditions.

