To overcome these lacunae and strengthen the diagnosis and research on fungal diseases in India with a focus on high throughput nonculture antigen, antibody, and molecular testing, the Indian Council of Medical Research (ICMR) has established 8 state-of-the-art Advanced Mycology Diagnostic and Research Centers (AMDRCs) in the country under ICMR-MycoNet Task Force Program. This national network of laboratories aims to improve human resources training and enhance fungal diagnostics, clinical care, research, and public health policies. The primary focus of all these centers is to create awareness of different fungal infections among the general population, develop research, cater diagnostic facilities to its catchment areas, and assess the impact of mycology laboratories on patient care and fungal mapping in the country. As an additional component of this Task Force project, it is proposed to develop a Web-based Mycology Inpatient Clinical Registry to perform prospective surveillance of all fungal infections among patients hospitalized at the ICMR AMDRCs in India. It aims to improve the knowledge gaps related to different fungal infections and understand current approaches to the diagnosis and treatment of invasive fungal infections (IFIs).

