### Aim and Objectives

The primary aim of the proposed study is to establish a national clinical registry in mycology to overcome the lack of knowledge on epidemiology, clinical course, and pathological characteristics of IFIs for evidence-based decision-making in clinical practice, public health programs and policy in the Indian context. The objectives of this study are to (1) develop advanced diagnostic facilities (culture, serology, molecular, therapeutic drug monitoring [TDM], and antifungal drug sensitivity test [AFST]) for fungal infections and a comprehensive digital clinical registry of IFIs; (2) describe the overall trends of fungal diseases, emerging fungal infections, and antifungal resistance; (3) map the distribution of fungi in the country through regional surveillance; (4) investigate the clinical features, diagnostics, treatment and patient outcomes among intensive care unit (ICU) patients with IFIs; (5) study the contribution of IFIs in the morbidity and mortality caused by different diseases in ICUs; and (6) investigate the clinical features, diagnostics, treatment, and outcomes among patients with chronic subcutaneous infections, such as mycetoma and chromoblastomycosis (neglected tropical diseases) [19].

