### Study Design

A hospital-based multicenter, prospective, noninterventional, observational clinical registry with prospective data collection through ICMR AMDRCs was established under the ongoing MycoNet Task Force project. The project duration is 5 years, with staggered entry of clinical sites following a standardized training and onboarding process.

This multicentric, Pan-India study was initiated with 5 AMDRCs in 2019. With a scope of increasing the number of reference centers in the next sequential phases of the Task Force project by the expert committee, 3 more centers were introduced and initiated in the financial year 2022-2023. Currently, the network has 8 AMDRCs dispersed across various regions of India. These AMDRCs include (1) All India Institute of Medical Sciences (AIIMS), Bhopal; (2) Assam Medical College and Hospital, Dibrugarh; (3) AIIMS, Bhubaneswar; (4) King George’s Medical University, Lucknow; (5) P.D. Hinduja Hospital, Mumbai; (6) AIIMS, New Delhi; (7) Nizam’s Institute of Medical Sciences, Hyderabad; and (8) St. John’s Medical College, Bengaluru. A timeline for the respective centers with a structural makeup is depicted in Figure 1. To develop a comprehensive network, apart from 8 data collection centers, Postgraduate Institute of Medical Education and Research, Chandigarh, for External Quality Assurance Scheme and laboratory training and ICMR-National Institute of Medical Statistics for data management have been included. ICMR is the overall coordinator of the project. The structural organization of ICMR-MycoNet is depicted in Figure 1. The network offers cutting-edge diagnostic tools for fungi, performs laboratory training to develop trained labor, investigates outbreaks, and conducts research on the epidemiology of fungi and antifungal resistance. The inclusion and exclusion criteria are given in Textbox 1.

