**Exclusion criteria**
Outpatient department or referral patients, patients who may be possible cases of invasive fungal infections, and patients without evidence of invasive disease or those with colonization only will not be included in the registry.Additionally, patients with superficial infections, infections limited to the skin, and allergic fungal diseases like allergic bronchopulmonary aspergillosis will be excluded.

Each team consists of a principal investigator from the mycology department and coprincipal investigators from different clinical divisions; including critical care; dermatology; ear, nose, and throat; hematology; infectious disease; internal medicine; and oncology to obtain patient samples. The AMDRCs also work closely with all ICUs, including hemato-oncology, trauma, respiratory, cardiac, and newborn care.

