A descriptive analysis of the pattern of clinical presentations by age, sex, and association with risk factors and comorbid conditions across urban and rural regions and states in India will be accomplished. Predictive factors for hospital clinical courses and outcomes will be derived for different treatment settings. The burden of IFIs and associated manifestations will be assessed using standard case definitions and reporting frameworks. Additionally, developing treatment guidelines will be aided by the pattern of comorbidities or risk factors affecting clinical recovery among with patients IFIs.

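### The registry claims national IFI frequency and outbreak signals in any region, but it enrolls only cases at 8 selected hospitals, with no described denominator and an undefined exclusion of referral patients

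*Protocol article*

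**What the plan says.** **Claims**

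- Discussion, Conclusions: it is imperative to "determine the frequency of occurrence of this condition in the country by establishing a registry". The following sentence puts forward this registry as the consequence. The Abstract's Background gives the same reason: data on the exact burden are lacking for India, hence the registry.
- Data Collection and Management: "The burden of IFIs and associated manifestations will be assessed using standard case definitions and reporting frameworks". Patterns of presentation "across urban and rural regions and states in India will be accomplished".
- Aim and Objectives, objective 3: "map the distribution of fungi in the country through regional surveillance".
- Abstract, Objective: the primary aim includes "early signals of any potential fungal outbreak in any region".

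**Design**

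- Study Design: a hospital-based registry. "Currently, the network has 8 AMDRCs dispersed across various regions of India". All eight are named.
- Introduction, Background: surveillance covers patients hospitalized at these centers.
- Inclusion criteria: ICU or other hospitalized patients with proven or probable IFI, plus all patients diagnosed with mycetoma or chromoblastomycosis.
- Exclusion criteria: "Outpatient department or referral patients", as well as possible cases. The article does not say what makes a patient a referral patient.
- Results: 531 IFI cases enrolled to date.

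**The concern.** A frequency needs a numerator and a denominator that refer to the same population. Here the numerator is cases at eight chosen hospitals. The article describes no catchment population, no count of admissions or ICU stays, and no sampling scheme that would let eight hospitals stand for the country. It is not a matter of detail left to an analysis plan, because no analysis of these records can supply a population that was never sampled.

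The outbreak claim has a similar gap. An area that sends no patients to any of the eight hospitals contributes no cases, whatever happens there. Cases from outside the host area would be seen mainly when patients are referred in, and referral patients are on the exclusion list.

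The article offers the registry as a basis for public health policy. Differences in case mix and testing between eight hospitals could then be read as geography, and an area with no data as an area with no disease.

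**Working it through.** The article states no incidence, precision target or detection threshold, so there is no figure of its own to reproduce. The check sets the claims against the sampling frame and adds two illustrations with labeled assumptions.

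**1. Frequency**

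Input from Results: x = 531 IFI cases at 8 sites, or 531 / 8 = 66.4 per site.

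Exact Poisson 95% limits for the count:

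- lower = χ²(0.025; 2x) / 2 = χ²(0.025; 1062) / 2 = 486.8
- upper = χ²(0.975; 2x + 2) / 2 = χ²(0.975; 1064) / 2 = 578.1

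Relative to 531 this is −8.3% to +8.9%, so chance variation is not the main difficulty.

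The rate is 1000 × 531 / D, where D is total admissions at the sites over the same period. D is not in the article, and the values below are assumptions:

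| Assumed D | Rate per 1000 | 95% limits |
|---|---|---|
| 50,000 | 10.62 | 9.74 to 11.56 |
| 100,000 | 5.31 | 4.87 to 5.78 |
| 200,000 | 2.66 | 2.43 to 2.89 |
| 500,000 | 1.06 | 0.97 to 1.16 |

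The estimate moves tenfold with D and by less than a tenth with sampling error. Knowing D would settle the rate at these eight hospitals. It would still not give a rate for India, because the hospitals were selected and not sampled.

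**2. Outbreak signals**

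Suppose an outbreak of N cases in an area, each reaching a registry site and being enrolled with probability c, independently. Take three enrolled cases as the smallest visible cluster. N, c and the threshold are all assumptions.

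P(at least 3) = 1 − Σ(k = 0 to 2) C(N, k) c^k (1 − c)^(N − k)

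| c | N = 50 | N = 100 |
|---|---|---|
| 0 | 0 | 0 |
| 0.1% | <0.01 | <0.01 |
| 1% | 0.01 | 0.08 |
| 5% | 0.46 | 0.88 |
| 10% | 0.89 | 1.00 |

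An area served by a center, with capture of 5 to 10%, can plausibly give a signal. An area with no center and capture near zero cannot.

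**3. The referral exclusion, read two ways**

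- *People or samples sent only for diagnosis and not admitted.* The exclusion then agrees with the inclusion criteria and with a registry of hospitalized patients. No inpatient is lost.
- *Patients transferred from elsewhere and then admitted.* These are hospitalized patients with proven or probable IFI, so the inclusion criteria take them and the exclusion criteria remove them. Capture from areas without a center then falls toward the top rows of the second table.

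The text does not decide between the two, and centers could apply it differently.

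**The case against.** The strongest reply is that this is largely a matter of wording.

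- The frequency sentence expresses a need. None of the six numbered objectives is incidence or prevalence, and the burden sentence does not say national. This stands in part. Even so, the Abstract and the Conclusions both give lack of such data as the reason for this registry, and readers will take the claim as a deliverable.
- Eight sites in different regions can describe which species and resistance patterns occur at each center, follow trends and flag clusters. Listing what occurs where needs no population denominator. This stands. A reader might infer from the design that the registry cannot map fungi or signal outbreaks at all. The article does not support that: what fails is the extension to the whole country and to any region.
- Referral may mean diagnosis-only referral, since it is paired with outpatients. This stands as a possible reading. A reader might infer that the exclusion certainly removes a large share of rural patients. The article gives neither the definition nor the share, so no size can be put on the loss.
- The stated purpose to "cater diagnostic facilities to its catchment areas" concerns the centers' diagnostic service, not registry coverage. This stands, and the point does not rest on it.
- The article admits regional limitations (Impact of AMDRCs) and plans more centers (Future Plan). The admission concerns territories that are hostile, poorly connected or thinly populated. It does not mention case-only enrollment or selected hospitals, and neither passage narrows the claims.
- Area of residence may already be on the case report form, which is not shown. This stands, so its absence is not alleged.

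**Conclusion.** The point holds for the claims of frequency in the country and outbreak signals in any region, and for burden and mapping where these are read as national. None of these can be obtained from a case-only registry at eight selected hospitals with no described denominator, and no later analysis changes that. In the illustration, the missing denominator alone leaves a tenfold range, against sampling error of about 9%. That range depends on the assumed admissions, but the conclusion does not.

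The referral exclusion is a real ambiguity of unknown size. On one reading it does no harm. On the other it contradicts the inclusion criteria and weakens regional coverage. Center-level description of species, resistance, trends and clusters among inpatients is unaffected by the point about claims.

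**What to change.** 1. **Restrict the claims.** In the Abstract's Objective, Aim and Objectives (objective 3), Data Collection and Management, and the Conclusions, limit frequency, burden, mapping and outbreak detection to inpatients at the participating centers. Drop the wording on frequency in the country and on any region.
2. **Mark unobserved areas.** On any map or regional table, show areas that contribute no patients as 'no data', not as zero.
3. **Define referral.** Reword the exclusion so that it covers only referred patients or samples not admitted at a center. Enter admitted referrals with a 'referred in' flag, and show results with and without them.
4. **Keep residence coarse.** Use area of residence only at a level compatible with the anonymization commitment under Ethical Considerations.
5. **Label rates.** If any rate is reported, use admissions and ICU stays per site over the same period as the denominator, and call it a hospital rate.

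The cost is more modest claims, one added flag and, only if rates are wanted, aggregate counts from each site. Records are anonymized without pseudonyms, so the flag may not be recoverable for cases already entered. Unless the form already holds it, those cases should be shown as referral status unknown. That is a reason to make the change early.

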## Appendix

Multimedia Appendix 1 Guidelines for invasive fungal infection (IFI) diagnosis for respective case definitions.

## Abbreviations

AFST: antifungal drug sensitivity test
AIIMS: All India Institute of Medical Sciences
AMDRC: Advanced Mycology Diagnostic and Research Center
CRF: case report form
EORTC/MSG: European Organization for Research and Treatment of Cancer and the Mycoses Study Group Education and Research Consortium
ICMR: Indian Council of Medical Research
ICU: intensive care unit
IFI: invasive fungal infection
TDM: therapeutic drug monitoring
WHO: World Health Organization
